## Abstract

**Background:**

Insomnia, defined as repeated difficulties getting or staying asleep, is common in the general population. Such sleep difficulties are a problem in their own right, but increasingly it is being recognised that they may also be a contributory factor in the development of a wide range of mental health problems. Our focus is upon the relationship between insomnia and psychotic experiences, such as paranoia and hallucinations. Psychotic experiences commonly occur in mild forms in the general population and have been linked to disrupted sleep. These psychotic-like experiences raise the risk of development of a clinical disorder. Our aim is to reduce insomnia in a large general population group, and examine the effect on paranoia and hallucinations at the age when mental health problems typically emerge. The primary hypotheses are that cognitive behaviour therapy (CBT) for insomnia will reduce insomnia and also levels of paranoia and hallucinations. The theoretical links will be substantiated by a planned mediation analysis. Improvements in a number of other mental health outcomes are also predicted.

**Methods/Design:**

We will carry out a parallel group, randomised controlled trial of 2,614 students with insomnia in universities across the UK. In the Oxford Access for Students Improving Sleep (OASIS) trial, participants will be randomised to digital CBT for insomnia (in addition to treatment as usual) or treatment as usual. Online assessments will take place at zero, three, 10 (post-treatment), and 22 (follow-up) weeks. Primary outcomes are insomnia and psychotic-like experiences (paranoia or hallucinatory experiences) at 10 weeks. Secondary outcomes are levels of mania, depression, anxiety, nightmares, psychological wellbeing, and the development of mental health disorders. All main analyses will be carried out at the end of the last follow-up assessment and will be based on the intention-to-treat principle. The trial is funded by the Wellcome Trust.

**Discussion:**

This study will be the first large-scale causal test of the relationship between sleep disturbance and psychotic experiences. It will provide evidence concerning the clinical effects of treating insomnia in young adults.

**Trial registration:**

This trial was registered with Current Controlled Trials (identifier: ISRCTN61272251) on 29 January 2015.

## Background

Disrupted sleep is increasingly recognised as a contributory causal factor in the occurrence of many mental health problems [1–3]. This is based not only upon the knowledge that sleep promotes better daytime functioning, but that sleep processes and mental health disorders have overlapping mechanisms. Our particular interest is in the potential causal relationship between poor sleep and psychotic experiences, such as paranoia and hallucinations. A key approach to establishing a causal relationship, called an interventionist causal model [4], is to manipulate a putative causal factor and assess the effect on the outcome of interest. In the current trial we aim to improve sleep in people with insomnia in order to examine the effect on psychotic-like experiences. This approach therefore informs both theory and clinical practice.

### Insomnia

The most common form of sleep disruption is insomnia, which principally comprises sustained difficulties in initiating or maintaining sleep. Insomnia is a common psychological disorder: at any one time, approximately one third of the general population experience symptoms of insomnia [5, 6], whilst around 6 % of adults will currently meet diagnostic criteria for insomnia disorder [5, 7]. Just as for other mental health problems, there is a spectrum of severity in the general population. Although prevalence is high, natural remission appears to be low. In one patient study, 74 % of individuals continued to have insomnia one year later, and 46 % reported insomnia persisting for over three years [8]. Importantly, meta-analyses report moderate to large sustained improvements in insomnia following treatment with cognitive behavioural therapy (CBT) for insomnia [9–11]. Thus clinical guidelines recommend the use of CBT for the treatment of insomnia [12, 13].

### Psychotic experiences

A focus upon explaining individual psychotic experiences has gained increased interest because of evidence that the main diagnoses of psychosis, such as schizophrenia, schizoaffective disorder, and delusional disorder, do not capture single disorders. The empirical research indicates that within these diagnoses are multiple (relatively) independent experiences, such as paranoia, hallucinations, grandiosity, thought disorder, and anhedonia [14–16]. Furthermore, these problems are not confined to clinical disorders. There is a spectrum of severity in the general population of each of these individual psychotic experiences. For example, many people have a few paranoid thoughts, and a few people have many severe paranoid thoughts [17–19]. Whilst these psychotic like experiences are often transitory, their persistence over time constitutes a risk factor for developing later psychosis [20].

### Insomnia and psychotic experiences

In cross-sectional and longitudinal studies, paranoia in particular [21–24], but also hallucinations [25] have been linked to insomnia. Circadian rhythm disruption has been shown to be common in patients diagnosed with schizophrenia [26–28]. Importantly, a recent twin study of adolescents indicates that insomnia and psychotic experiences share overlap in genetic and environmental aetiology [25]. Applying the interventionist-causal model approach, we showed in a pilot case series that treating insomnia with CBT in patients with persecutory delusions (that is, severe paranoia) is associated with reductions in insomnia, paranoia, and anomalous perceptual experiences [29]. This is consistent with insomnia having a contributory causal role in psychotic experiences. Developing this work, we are completing a randomised controlled trial testing CBT for insomnia in 50 patients with delusions and hallucinations [30].

In the current trial we set out to test the effects of treating insomnia on psychotic-like experiences (and other mental health outcomes) in students attending university. A systematic literature search indicated that there had been no such similar tests. The benefit of choosing this participant group to test the hypotheses is twofold. First, it will enable recruitment of a large sample to test the hypotheses robustly. Circular emails will be sent at many UK universities, and students will be able to carry out the study online without face-to-face contact with the research team. Second, mental health problems such as psychosis typically have their first onset in late adolescence or /early adulthood [31], and therefore university students are at a vulnerable, and hence important, age to study. We will treat insomnia using the recommended approach of CBT. The CBT course will be delivered entirely online using computer or smartphone [32, 33]. It will be compared with treatment as usual, rather than an attention control or active control, because our central aim is to manipulate sleep to test the effects on mental health problems, that is, to conduct a mechanistic test. We therefore require one group to exhibit a change sleep patterns, and one group to show less change in sleep patterns. Furthermore, the CBT intervention to be used has already been shown to be of much greater efficacy than an attention control condition [32].

The primary hypotheses for the trial are:The digital CBT intervention will reduce insomnia by the end of treatment (10 weeks).The digital CBT intervention will reduce psychotic-like experiences (paranoia and hallucinations) by the end of treatment.Changes in insomnia will mediate the changes in psychotic-like experiences.

The secondary hypotheses are:The digital CBT intervention will reduce levels of depression, anxiety, nightmares, and mania by the end of treatment (10 weeks).The digital CBT intervention will improve psychological wellbeing by the end of treatment.The effects of CBT will be maintained at the scheduled follow-up assessment (22 weeks).The digital CBT intervention will lead to the occurrence of fewer mental health disorders during the period of the trial, as assessed by screening tools at 22 weeks for ultra-high risk of psychosis, bipolar affective disorder, depression, and anxiety, and by treatment by mental health services.

## Methods/Design

### Research design

The study is a parallel group, superiority, randomised controlled trial of digital CBT in addition to treatment as usual versus only treatment as usual. The trial design is summarised in Fig. 1. The study will be carried out completely online. Participants will carry out screening, informed consent, assessments, allocation to condition, and intervention via a computer programme specifically designed for the trial. We will therefore run an internal pilot of 100 participants in order to check that the automated computer system is running correctly. The study has received ethical approval from the University of Oxford Medical Sciences Inter-Divisional Ethics Committee (reference number: MSD-IDREC-C2-2014-034). An information sheet is provided online, and informed consent is completed online before participation in the study can occur.

**Fig. 1 Fig1:**
[figure not shown]
Summary of the trial design for the OASIS study

### Participants

We will recruit 2,614 students from UK universities. The inclusion criteria are: those with a positive screen for probable insomnia disorder, as indicated by a score of 16 or lower on the Sleep Condition Indicator (SCI) [34]; and being aged 18 or older. There are no exclusion criteria; we will not omit participants who report no signs of psychotic-like experiences because the dimensional measures of paranoia and hallucinations will be endorsed to some extent by a majority of participants, while we are also interested in other mental health outcomes that will be relevant to all participants (for example psychological wellbeing). Universities across the UK will be approached to take part. At each university, participants will be recruited via email circulars, which will provide a link to the web-based screening. Therefore many thousands of students at each university taking part will receive an invite to take part in screening for the study. Participants will not be recruited via health settings.

### Randomisation and allocation concealment

This study will use simple randomisation with an allocation ratio of 1:1, as recommended for large clinical trials [35]. It will be carried out by the automated online system, hence the research team will be unable to influence randomisation, and have no access to future allocations.

### Blinding

This will be a single blind trial. Assessments will be self-reported and carried out online, and hence the research team will be blind to outcomes during the trial. Participants will be informed of their randomisation outcome by an automatic email, and hence they will not be blind to treatment allocation. It is notable that the research team is unlikely to have any contact with research participants, and will therefore be unable to bias the allocation or assessments. If participants do contact the team and reveal the allocation, the absence of assessments carried out by an assessor prevents assessments becoming unblinded.

### Assessment points

Assessments will take place at the key assessment points of 0 (baseline), three (mid-therapy), 10 (end of therapy), and 22 weeks (follow-up). As an ethical consideration, all the control participants will be provided with CBT at 23 weeks, once the 22-week follow-up assessment has been conducted. We will therefore take this opportunity to include a further follow-up at 33 weeks for all trial participants (providing a potential replication of the within group treatment effect).

### Planned intervention

The CBT for insomnia intervention is delivered predominately via the internet. The delivery is structured into six sessions, lasting an average of 20 minutes each. The course takes a minimum of six weeks to complete, with sessions unlocked weekly. Participants can move at a slower pace, for up to a maximum of 12 weeks. All participants have to at least start the programme online. Certain tools (such as sleep diaries and relaxation audios) can also be accessed using the web browser of any smartphone. All of the six core sessions, sleep diaries, relaxation audios, and the scheduling tool can also be accessed using an iOS app, but this is only an option for participants who have an iPhone®. The treatment content is based on CBT for insomnia manuals [36–38] and includes a behavioural component (sleep restriction, stimulus control, and relaxation), a cognitive component (paradoxical intention, cognitive restructuring, mindfulness, positive imagery, and putting the day to rest) and an educational component (psycho-education and sleep hygiene).

The programme is highly interactive, and content is presented by an animated virtual therapist. Participants make a time for the session and are prompted via email and/or SMS if they do not ‘attend’. Participants complete daily sleep diary information throughout the intervention, which are used by the programme to provide tailored, personalised help. Participants receive an email and/or SMS reminder each morning to prompt them to fill in their sleep diary. In addition, participants complete a short questionnaire at the beginning of therapy to set treatment goals. Throughout the course of therapy, participants have access to a moderated online community and an online library of information about sleep. Participants can view their online case file, which includes four sections: a progress review, a reminder of strategies to try out between sessions, an agreed sleep schedule, and a list of further reading. The system provides online analytics, which can be used to monitor adherence by assessing how many sessions were completed and the number of weeks to complete the course. Data from the CBT programme show that 90 % of participants complete the course within 10 weeks; participants will have access to the intervention for up to 12 weeks. We note that treatment as usual will actually comprise of no intervention at all for the majority of participants, since they are not being recruited from clinical services.

### Outcome measures

Participants will receive an email prompt to complete the assessments online. The order of the assessments will be consistent across all participants and all time points. If participants do not complete the questionnaire within two days they will receive an email reminder. The full battery of questionnaires comprises 118 questions in total. The week three assessment is briefer, including only the key measures, which total 44 questions.

The primary measure for insomnia is the SCI [34]. This is an eight-item measure. Scores can range from 0 to 32, with higher scores indicating better sleep. A clinical cut off of less than 17 has been shown to correctly identify 89 % of those with probable insomnia disorder. The measure has good internal consistency (Cronbach’s alpha = 0.86) [34]. We will use a version of the SCI that includes one additional question regarding early morning waking.

The primary measure for paranoia will be the Green *et al.* Paranoid Thoughts Scale (GPTS), Part B [39]. The GPTS assesses persecutory ideation and the timeframe used will be the past fortnight. The scale comprises 16 items, each rated on a one (not at all) to five (totally) scale. The persecutory ideas sub-scale has excellent internal consistency (Cronbach’s alpha = 0.90), good test re-test reliability (correlation coefficient = 0.81), and good convergent and criterion validity [39].

The Specific Psychotic Experiences Questionnaire (SPEQ) - Hallucinations sub-scale [16] will be the primary outcome for hallucinatory experiences. The scale is adapted from the Cardiff Anomalous Perceptions Scale [40], and comprises nine items measuring hallucinatory experiences across a range of sensory modalities and has good internal consistency, test re-test reliability, and convergent validity [16]. Participants will be asked to consider the period of the past fortnight and the scale used for each item is from zero (not at all) to five (more than once per day).

Secondary outcome measures for sleep include the Insomnia Severity Index [41, 42] and the Disturbing Dreams and Nightmare Severity Index [43]. We will also include in the assessment one question concerning chronotype from the Morningness-Eveningness Questionnaire [44]. A secondary outcome measure for psychotic-like experiences will be the 16-item version of the Prodromal Questionnaire [45]. A score of six or more has 87 % specificity and 87 % sensitivity to correctly classify ultra-high risk for psychosis mental states in a help-seeking sample [45]. The measures to assess affective symptoms will be the Patient Health Questionnaire (PHQ) nine-item version [46], the Generalised Anxiety Disorder (GAD) seven-item version [47], the PHQ four-item version for a brief mid-therapy assessment [48], and the Altman Mania Scale [49].

To test the hypothesis concerning the potential development of mental health disorders by 22 weeks, specifically meeting criteria for ultra-high risk for psychosis, bipolar affective disorder, depression, and anxiety, we will use established cut-offs on the Prodromal Questionnaire [45], Altman Mania Scale [49], PHQ [46], and GAD-7 [47], respectively. Participants will be asked at each online assessment time point (apart from week three) whether they are in contact with mental health services, have received a mental health diagnosis, take medication for a mental health problem, or are currently receiving psychological therapy. We will additionally administer the Warwick Edinburgh Mental Wellbeing Scale [50], the Work and Social Adjustment Scale [51], and gather information on the demographics of the sample.

### Assessment of safety

The likelihood of serious adverse events occurring during this trial is low since CBT for insomnia has not been reported to cause them. The intervention offered in the trial has previously been tested in a randomised controlled trial testing change in insomnia and no adverse outcomes were reported [32]. We will record the occurrence of any serious adverse events in trial participants, defined as: all deaths, suicide attempts, serious violent incidents, admissions to secure units, and formal complaints about the online intervention. Owing to the online nature of the assessments and intervention, it is unlikely that the research team will become aware of all such events. Adverse events are likely to come to our attention only if we are contacted by a trial participant. For participants concerned about their mental health, a list of UK support services is provided on the study website. If a participant makes contact via email or telephone then the clinical psychologist coordinating the trial can advise on appropriate clinical services.

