After randomisation, participants will be analysed according to their allocated treatment group, irrespective of what treatment they actually receive. We will endeavour to obtain full follow-up data on every participant to allow full intention-to-treat analysis but we will inevitably experience the problem of missing data due to withdrawal, loss to follow up, or non-response questionnaire items. Data analysis will be performed using a mixed-effect model for repeated measures. The model will include treatment group, time, treatment-by-time interaction, and baseline covariates. An unstructured correlation matrix will be used to model the within-subject error correlation structure. An appropriate contrast will be specified to test for treatment efficacy between randomised groups for the primary outcome. We will also perform various sensitivity analyses using imputation methods to test whether the results are robust enough to allow for different assumptions about the missing data. The results from the trial will be prepared as comparative summary statistics (difference in response rate or means) with 95 % confidence intervals. All the tests will be done at a 5 % two-sided significance level. The study results will be reported in accordance with the Consolidated Standards of Reporting Trials (CONSORT) 2010 statements [53, 54] and Standard Protocol Item: Recommendations for Interventional Trials (SPIRIT) [55, 56] guidelines.

We will use modern causal inference methods for mediational analyses [57, 58]. This involves using parametric regression models to test for mediation of the digital CBT intervention on psychotic-like experiences through insomnia. Analyses will adjust for baseline measures of the mediator, outcomes, and putative measured confounders. We will include repeated measurement of mediators and outcomes to account for classical measurement error and baseline confounding, and instrumental variable methods (baseline covariate by randomization interactions as potential instruments) to investigate the sensitivity of the estimates to these problems and that of unmeasured confounding [57]. A full, detailed analysis plan, including plans for any interim analysis, subgroup analysis, and sensitivity analysis of the primary outcomes, will be prepared and finalised before the analysis.

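### The closed list of serious adverse events counts formal complaints about the programme, which through week 22 can arise from use only in the CBT arm, and omits psychiatric admissions to non-secure wards

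*Protocol article*

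**What the plan says.** Under Assessment of safety, the protocol article undertakes to record serious adverse events and defines them as "all deaths, suicide attempts, serious violent incidents, admissions to secure units, and formal complaints about the online intervention". The list is introduced as a definition, not as a set of examples. The same section concedes limited capture: "Adverse events are likely to come to our attention only if we are contacted by a trial participant".

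The arms are "digital CBT in addition to treatment as usual versus only treatment as usual" (Research design). Under Planned intervention the article adds that "treatment as usual will actually comprise of no intervention at all for the majority of participants". Under Assessment points, "all the control participants will be provided with CBT at 23 weeks, once the 22-week follow-up assessment has been conducted".

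Under Outcome measures, participants in both arms are asked at every assessment except week three "whether they are in contact with mental health services, have received a mental health diagnosis, take medication for a mental health problem", and also whether they are receiving psychological therapy. One secondary hypothesis is that CBT leads to "fewer mental health disorders during the period of the trial, as assessed by screening tools at 22 weeks" and by treatment from mental health services.

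On reporting, the statistical section says in general terms that "The results from the trial will be prepared as comparative summary statistics" with 95 % confidence intervals. It does not mention serious adverse events.

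**The concern.** The definition has two separate weaknesses.

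- **A one-arm, non-health item.** A formal complaint about an online course measures dissatisfaction, not harm. During the randomised period only the CBT arm uses the course. If the listed events were added up and shown by arm, the CBT total would include a component to which the control arm is not exposed.
- **A narrow admission item.** The trial studies paranoia, hallucinations, mania and depression in young adults, with no exclusion criteria. Admission to an ordinary psychiatric ward with a psychotic or manic episode would be among the more informative safety events. Read literally, the list does not count it, while it does count a complaint about the software.

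What is at stake is whether the safety record can be interpreted. The efficacy outcomes are not affected.

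**Working it through.** The article states no serious adverse event rate, count or test, so there is no figure to reproduce. The check sets the sections side by side and then uses assumed counts to show direction.

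**Step 1: who can generate each listed item through week 22?**

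| Listed item | CBT arm | Control arm |
|---|---|---|
| Death | yes | yes |
| Suicide attempt | yes | yes |
| Serious violent incident | yes | yes |
| Admission to a secure unit | yes | yes |
| Formal complaint arising from use of the programme | yes | no, access starts at week 23 |

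Four items are open to both arms and one is not. A control could conceivably complain about a programme that he or she has not used, but not from exposure to it. After week 23 controls can also complain from use, so the asymmetry belongs to the randomised comparison, not to the extra follow-up at 33 weeks.

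**Step 2: capture.** Events reach the team mainly when a participant makes contact. A formal complaint is itself a contact, whereas a clinical event becomes known only if someone reports it. Complaints may therefore form a larger share of the known events than of the events that occur. This is reasoning from the text; the article gives no figure.

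**Step 3: illustration of a pooled count by arm.** The planned 1,307 per arm comes from the sample size paragraph. The event counts are assumptions with no basis in the article: *b* = 3 clinical events in each arm and *c* complaints in the CBT arm only. With equal arms, risk ratio = (*b* + *c*)/*b*.

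| *c* (as % of 1,307) | CBT v control | Risk ratio | Fisher exact p |
|---|---|---|---|
| 0 (0 %) | 3 v 3 | 3/3 = 1.0 | 1.00 |
| 2 (0.15 %) | 5 v 3 | 5/3 = 1.7 | 0.73 |
| 5 (0.38 %) | 8 v 3 | 8/3 = 2.7 | 0.23 |
| 10 (0.77 %) | 13 v 3 | 13/3 = 4.3 | 0.02 |

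Clinical harm is equal in every row. With complaints counted apart, each row is 3 v 3. The direction is fixed by the definition, but the size depends entirely on *c* and *b*, which are unknown.

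**Step 4: can a non-secure psychiatric admission enter the record another way?**

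- *Through another listed item:* yes, if it involves a suicide attempt or a serious violent incident. An admission for psychosis or mania without either does not enter.
- *Through the outcome questionnaires:* partly. Service contact, diagnosis, medication and therapy are asked about in both arms, but no admission item is named, and the answers are not linked to the serious adverse event definition. An admitted student who completes an assessment may appear as a service contact, indistinguishable from an outpatient.

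**The case against.** The strongest reply is that the article plans only to record these events. No section specifies a pooled total, a rate by arm or a test, and the general sentence on comparative summaries does not name serious adverse events. How they are tabulated is commonly left to the full protocol or analysis plan. If events are listed by type, complaints remain visible and distort nothing. This stands, and it limits the first weakness to any pooled count that might be shown by arm.

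Three stronger readings are tempting, and the document supports none of them.

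- *That complaints will multiply the CBT total severalfold.* The article gives no complaint rate. It also describes contact with the team as unlikely and the likelihood of serious adverse events as low. The larger ratios above follow from assumed counts only.
- *That the safety record is biased in favour of the intervention.* The complaint item errs against CBT. It can overstate harm but cannot conceal it.
- *That the trial cannot register serious psychiatric harm.* Suicide attempts, serious violent incidents and secure-unit admissions count. Service contact and screening measures for psychosis risk, mania and depression are collected in both arms.

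It is also fair to say that the article does not define a secure unit, so the exact reach of that item cannot be settled here, and that passive capture is probably the larger weakness.

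None of this removes the point. The list is stated as a definition, so the criticism concerns what is written, not detail left out. Tabulation by type would expose the complaints, but it would not recover admissions that the definition never counts.

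**Conclusion.** The point holds as a fault in the stated definition. The list mixes clinical events with a non-health item that, through week 22, can arise from use of the programme only in the CBT arm, and it omits psychiatric admissions to non-secure wards unless another listed event applies.

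The conclusion rests on reading the list as closed, as its wording indicates, and on controls having no access before week 23. The first part matters only if events are pooled by arm, and its size is unknown. The second part does not depend on how events are tabulated, but the number of admissions missed is also unknown. Priority is minor to moderate: no primary or secondary outcome changes, and passive capture limits what a better definition can achieve.

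**What to change.** Amend the definition and its reporting as follows:

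1. Take formal complaints out of the serious adverse event list and report them on a separate line as feedback on the programme.
2. Widen the admission item to any psychiatric admission, whether or not the unit is secure.
3. Tabulate serious adverse events by type and by arm, so that no reader has to rely on a single total.

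The cost is about one sentence in the safety section and one extra line in the safety table, plus slightly more events to log under the broader admission item. Treatment, randomisation, sample size and efficacy analyses do not change. The fix does not cure passive capture, which should still be stated as a limitation when the safety results are reported.

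### Serious adverse events are captured passively although scheduled questionnaires could ask about them, and the definition includes a category that before week 23 can in practice arise only in the CBT arm

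*Protocol article*

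**What the plan says.** The section Assessment of safety sets the commitment: "We will record the occurrence of any serious adverse events in trial participants, defined as: all deaths, suicide attempts, serious violent incidents". The list goes on to admissions to secure units and "formal complaints about the online intervention". The same paragraph then concedes, giving the online format as the reason, that "it is unlikely that the research team will become aware of all such events", and describes how events will reach the team: "Adverse events are likely to come to our attention only if we are contacted by a trial participant". The section Blinding adds that "the research team is unlikely to have any contact with research participants".

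The trial nevertheless has regular contact with participants through its own system. The abstract gives the schedule: "Online assessments will take place at zero, three, 10 (post-treatment), and 22 (follow-up) weeks". The section Outcome measures describes an email prompt for each assessment and a reminder after two days without completion. It also says: "Participants will be asked at each online assessment time point (apart from week three) whether they are in contact with mental health services". That block goes on to mental health diagnosis, medication and psychological therapy. None of the listed serious adverse events is named in it, and it is not linked to safety recording.

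On when controls receive the programme, the section Assessment points says that "all the control participants will be provided with CBT at 23 weeks", after the 22-week assessment.

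**The concern.** The method of capture cannot deliver the commitment. A promise to record all deaths and suicide attempts is paired with a route that depends on an unprompted message from the person affected, in a trial built to run with almost no contact between team and participant. A participant cannot report their own death, and nothing in the text prompts anyone to report the other events.

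The trial has no exclusion criteria, selects people for insomnia and has paranoia and hallucinations among its primary outcomes. The same section supports its expectation of low risk by noting that an earlier trial of the intervention reported no adverse outcomes. A near-empty count from passive capture could be added to that record and taken as reassurance when it says little either way. Pooling complaints about the programme with clinical events would blur the count further, because only one arm has a programme to complain about during the randomised comparison.

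**Working it through.** The protocol gives no event rate, capture rate or safety power figure, so there is no stated figure to reproduce. The check has three parts.

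**1. Commitment against method.** Commitment: any serious adverse event, all deaths. Method: likely to be known only through participant contact. Existing structured channel: prompted questionnaires with a service-contact block at weeks 0, 10 and 22 (not week 3). As described, that block would not identify a suicide attempt or a violent incident, and would show a secure-unit admission only indirectly. The existing items are therefore not a substitute; the point is that the channel exists and could carry direct items.

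**2. Illustration of the undercount.** Inputs from the section Statistical analysis and sample size: N = 1,307 per arm and 40% expected attrition, so 60% assumed to respond. Assumptions not in the document: true risk p over the trial, and share q of events reported spontaneously.

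- Contact alone: N × p × q.
- Direct questions added: N × p × (0.6 + 0.4q).

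With p = 1%, the true number is 1,307 × 0.01 = 13.1 per arm.

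| q | Contact alone | Direct questions added |
|---|---|---|
| 10% | 13.07 × 0.10 = 1.3 | 13.07 × 0.64 = 8.4 |
| 25% | 13.07 × 0.25 = 3.3 | 13.07 × 0.70 = 9.1 |
| 50% | 13.07 × 0.50 = 6.5 | 13.07 × 0.80 = 10.5 |

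Over the same range of q, p = 0.1% (1.3 true events) gives 0.1 to 0.7 against 0.8 to 1.0, and p = 2% (26.1 true events) gives 2.6 to 13.1 against 16.7 to 20.9. The right-hand figures are optimistic. They assume that every event can be self-reported, that every responder discloses, and that non-response is unrelated to having had an event.

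**3. Comparability of arms.** Let E be the clinical events seen in each arm under equal risk and equal reporting, and C the formal complaints. Up to week 22 the pooled count is E + C in the CBT arm and E in the control arm. The asymmetry follows from the definition and the week-23 crossover, whatever the reporting behaviour.

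For the clinical events alone, with equal true risk, the observed ratio of CBT to control is (N × p × q₁)/(N × p × q₀) = q₁/q₀. Reporting shares of 25% and 25% give 1.0; 50% and 25% give 2.0; 10% and 20% give 0.5. The document does not say which, if any, of these applies.

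**The case against.** The strongest reply is that the limitation is disclosed. The protocol does not present its count as complete, describes no between-arm test of these events, and can properly leave tabulation to an analysis plan that is not shown. Worsening mental health is also measured actively in both arms, through the Prodromal Questionnaire, PHQ, GAD-7 and Altman Mania Scale with cut-offs at 22 weeks, and through the service-contact items. The remedy is partial too: it cannot reach deaths or non-responders, and it creates positive answers that an automated trial must deal with.

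Much of this stands. It limits the point to ascertainment and reporting and leaves the efficacy inference untouched. It does not remove the point. Disclosing an avoidable gap does not close it, symptom scales do not count suicide attempts, violent incidents or admissions as events, and the capture route is fixed in this text.

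A reader might infer more than the document supports:

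- That every participant answers the weeks 10 and 22 items. They are asked; 40% attrition is expected.
- That the protocol admits most events will be missed, or that counts will be too low by a known margin. It concedes only that not all will be known, and qualifies the contact route as likely.
- That the arms report differently. Participants know their allocation, and CBT users have a moderated online community, so this is plausible. But the contact route in the safety section is described without distinction by arm, and any bias could run in either direction.
- That a power to detect a safety difference can be quoted. It would rest on invented rates and, under passive capture, on a handful of events.

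**Conclusion.** The point holds as a limited design weakness. Capture of serious adverse events is passive and admittedly incomplete, although a prompted questionnaire system that could carry direct questions already runs in both arms. That counts will fall short is as good as certain, since the protocol itself expects not to learn of every event. By how much is unknown, and the counts in the working are illustrations that depend wholly on the assumed p and q. The pooled definition is structurally asymmetric up to week 22 through the complaints category alone; any other difference in reporting between arms is possible but not shown. As planned, the counts should not be read as rates or compared between arms without that caveat.

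**What to change.** Add brief yes/no items to the week-10 and week-22 questionnaires for the listed categories that a participant can report (suicide attempt, serious violent incident, secure-unit admission), worded identically in both arms. Report solicited events by arm with the number who responded, and show spontaneous reports separately. List formal complaints apart from clinical events and outside any comparison of arms. State in the report that deaths and events in non-responders remain under-ascertained, so a low count is not evidence of safety.

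The cost is a few more questions in a battery of 118, a slight extra burden on participants and an ethics amendment. The investigators must also settle, before the items go live, how positive answers are handled; the safety section currently describes only a list of support services and advice to participants who make contact. Treatment and the efficacy analyses do not change.
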